**1.2.1 Objectives**

The primary objective is to quantify the psychological burden and the effect on health-related quality of life (HRQoL) of hospitalization during the pandemic, in terms of anxiety, depression and post-traumatic stress disorder, 1 month, 3 months and 12 months after discharge. Secondary objectives are 1) to examine possible differences between COVID-19 and non-COVID-19 patients and 2) to examine possible differences between COVID-19 ICU patients and COVID-19 non-ICU patients.

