**1.3.4 Participants timeline**

All patients admitted to the hospital with a suspicion of COVID-19 are registered in the International Severe Acute Respiratory and emergency Infection Consortium (ISARIC, Oxford, United Kingdom) and Castor EDC (Castor EDC, Amsterdam, the Netherlands). Eligible patients are approached 1 month after discharge from the hospital by sending an information letter explaining the nature and aim of the study accompanied by the first set of questionnaires. Participation in the questionnaire takes approximately 15 minutes. Since participation requires only a limited amount of effort and time, the standardized informant-consent procedure was simplified. At the beginning of the questionnaire, patients are asked for consent to use the data gathered using the questionnaires. Patients who agree to participate receive the second set of questionnaires 3 months and 12 months after hospital discharge by e-mail or postal mail, depending on the stated preference. Patients who do not want to participate are asked to return the questionnaire empty. All non-responders are called two weeks after sending the questionnaire as a reminder. Non-responders unable to be reached by telephone are send the second and third questionnaire. Patients who deny participation either via telephone or by returning an empty questionnaire, are excluded from further follow-up.

Data gathered using the questionnaires will be anonymized and will not have an influence on the standard hospital care of these patients in any way possible.

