**1.4 Methods: data collection, management, analysis**

**1.4.1 Data collection Methods**

All data will be collected using electronic data capture system Castor EDC (Castor EDC, Amsterdam, the Netherlands) and International Severe Acute Respiratory and emergency Infection Consortium (ISARIC, Oxford, United Kingdom).

Demographic and treatment related characteristics will be retrieved from patients records and include age, gender, ethnicity, BMI, employment as healthcare worker, medical history, hospital length of stay, ICU admission, ICU length of stay, diagnosis COVID-19; SOFA score, P/F ratio and S/F ratio at first day of COVID-19 suspicion; need and duration of oxygen therapy, non-invasive ventilation, invasive ventilation and prone positioning and insertion of tracheostomy. Educational level, employment status and the psychiatric history will be additionally assessed using a self-composed questionnaire.

Symptoms of PTSD are assessed using the Impact of Event Scale – Revised (IES-R). The IES-R is a validated 22-item questionnaire and assesses subjective distress caused by a traumatic event. The IES-R yields a total score (ranging from 0 to 88, higher scores indicating more severe symptoms) and subscale scores can be calculated for symptoms of intrusion, avoidance, and hyperarousal. A total IES-r score above 24 is classified as clinically significant symptoms of PTSD.^18,19^

Symptoms of depression and anxiety are assessed using the Hospital Anxiety and Depression Scale (HADS). The HADS is commonly used to determine the levels of anxiety and depression that a person is experiencing. The HADS is 14-item scale that generated ordinal data. Seven of the items relate to anxiety and seven relate to depression. The HADS yields a depression and anxiety sum score, ranging from 0 to 21 with higher scores indicating more severe symptoms. A sum score above 8 of either the depression or anxiety subscale is classified as clinically significant symptoms of depression or anxiety.^20,21^

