**1.4.3 Statistical Methods**

Baseline demographics will be communicated using descriptive statistics. Continuous variables will be presented as mean (SD) when normally distributed and as median (IQR) when not normally distributed. Categorical variables will be presented as absolute number and relative frequency.

Patients will be stratified based on the confirmation of the diagnosis COVID-19 and, within the COVID-19 patients, on necessity for ICU treatment. Differences between stratifications will be analyzed using a Standard Student’s T-test if the residuals are normally distributed or using a Mann-Whitney U test when the residuals are not normally distributed. Differences in categorical variables will be analyzed using a Chi-squared test or, in case of small sample sizes, a Fisher’s exact test.

Missing data will not be imputed due to the observational nature of the study.

All analyses will be performed using SPSS (version 24.0; SPSS Inc., Chicago, IL) and R for Statistics (R Foundation for Statistical Computing, Vienna, Austria, 2015). A P-value ≤0.05 will be considered statistically significant.

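### Imputation is ruled out for a reason that does not support it, and the analyses named leave the burden estimates open to selective questionnaire response

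*Protocol*

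**What the plan says.** Protocol section 1.4.3 deals with missing data in one sentence: "Missing data will not be imputed due to the observational nature of the study". The analyses it names are descriptive statistics, the t-test or Mann-Whitney test, and the chi-squared or Fisher's exact test.

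The estimates affected are the primary ones. Section 1.2.1 says: "The primary objective is to quantify the psychological burden and the effect on health-related quality of life (HRQoL) of hospitalization during the pandemic", at 1, 3 and 12 months. Section 1.4.1 turns the scores into case classifications: "A total IES-r score above 24 is classified as clinically significant symptoms of PTSD", and for the HADS, "A sum score above 8 of either the depression or anxiety subscale is classified as clinically significant symptoms of depression or anxiety". The protocol does not use the word prevalence, but proportions above these cut-offs follow naturally, next to mean or median scores.

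Section 1.3.4 describes how the outcomes are obtained. The first contact is by letter: "Eligible patients are approached 1 month after discharge from the hospital by sending an information letter". There are two measures against non-response: "All non-responders are called two weeks after sending the questionnaire as a reminder", and "Non-responders unable to be reached by telephone are send the second and third questionnaire". Patients who decline leave follow-up.

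The same section says of the source population: "All patients admitted to the hospital with a suspicion of COVID-19 are registered". Under section 1.4.1, age, gender, medical history, ICU admission, length of stay, SOFA score and ventilation come from patient records, not from the questionnaire.

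**The concern.** The protocol fixes a rule and gives one reason for it, and the reason does not carry the rule. Whether to impute depends on the amount of missing data, the mechanism behind it and the auxiliary information available. Whether treatment was assigned or merely observed has no bearing on any of these. If anything, a cohort whose outcomes come only from voluntary questionnaires over 12 months is a setting where the question matters.

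Willingness to answer questions about trauma, anxiety and depression may plausibly vary with severity of illness, recovery and the symptoms themselves. Tests and summaries that use observed values only then estimate the burden among those who replied, which can differ from the burden among those hospitalised. If response patterns differ by COVID-19 status or ICU stay, the two secondary comparisons are affected as well. Record data that could be used to examine and partly adjust for this are already collected.

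**Working it through.** The protocol gives no sample size, expected response or expected prevalence, so there is no figure of its own to reproduce. **Every input below is an assumption**, chosen to show the mechanism.

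**1. General size of the bias.** Let r be the response proportion.

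Bias of the respondents-only estimate = (1 − r) × (prevalence in responders − prevalence in non-responders).

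| Response r | Non-responders 10 points higher | Non-responders 20 points higher |
|---|---|---|
| 40% | 0.6 × (−10) = −6 points | 0.6 × (−20) = −12 points |
| 60% | 0.4 × (−10) = −4 points | 0.4 × (−20) = −8 points |
| 80% | 0.2 × (−10) = −2 points | 0.2 × (−20) = −4 points |

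If non-responders have the lower prevalence, the sign reverses.

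**2. Response that depends on a recorded variable (missing at random given ICU stay).** Assume 20% ICU patients, prevalence 40% in ICU and 20% in non-ICU patients, response 40% in ICU and 70% in non-ICU patients.

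- True prevalence: 0.20 × 0.40 + 0.80 × 0.20 = 0.08 + 0.16 = 24.0%.
- Responding share: 0.20 × 0.40 + 0.80 × 0.70 = 0.08 + 0.56 = 0.64.
- Cases among responders: 0.08 × 0.40 + 0.56 × 0.20 = 0.032 + 0.112 = 0.144.
- Respondents-only prevalence: 0.144 / 0.64 = 22.5%, which is 1.5 points too low.
- Weighted by 1/response within ICU stratum: 0.032/0.40 + 0.112/0.70 = 0.08 + 0.16 = 24.0%. The true value is recovered.

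**3. Response that depends on the symptom itself (missing not at random).** Assume a true prevalence of 20%. Observed prevalence = p·a / (p·a + (1 − p)·b), where a and b are the response proportions in symptomatic and asymptomatic patients.

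- a = 40%, b = 60%: 0.08 / (0.08 + 0.48) = 14.3%.
- a = 60%, b = 40%: 0.12 / (0.12 + 0.32) = 27.3%.

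Weighting on record variables corrects these figures only as far as those variables explain the link between symptoms and response. If they explain none of it, 14.3% stays 14.3%.

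**4. Group comparison.** Assume a true prevalence of 30% in both groups, with response (symptomatic, asymptomatic) of 70% and 60% in one group and 50% and 60% in the other.

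- First group: 0.21 / (0.21 + 0.42) = 33.3%.
- Second group: 0.15 / (0.15 + 0.42) = 26.3%.

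A difference of 7 points appears where none exists. Response here again depends on symptoms, so the caveat in step 3 applies.

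**5. Skipped items.** The rule read literally would also cover single items. At an assumed independent 2% skip rate per item, complete totals are 0.98^22 = 64.1% for the 22-item IES-R and 0.98^7 = 86.8% for a seven-item HADS subscale. At 1% they are 80.2% and 93.2%.

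**The case against.** **The sentence bars imputation only.** A reader might infer that the protocol forbids any handling of missing data. It does not. Weighting, likelihood-based models, responder comparisons and scoring rules are simply not mentioned, and a statistical analysis plan that is not shown may contain them. This stands, and their absence is not the point made here. The point is a rule the protocol itself states, on a reason that does not support it. A later plan cannot impute without contradicting that rule.

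**Available-case analysis is not wrong in itself.** This also stands. It can be a defensible choice, but it needs a reason that bears on missingness.

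**The study already acts against non-response.** The reminder call and the continued mailing to patients not reached deserve credit. They lower 1 − r in the bias formula, but they do not bring it to zero, and patients who decline leave follow-up.

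**The larger figures are not what an adjustment would recover.** A reader might take 14.3% or 27.3% as the error that weighting would remove. Those figures assume response driven by the symptom itself, which weighting and standard imputation do not fully correct. In addition, educational level, employment status and psychiatric history come from the questionnaire (section 1.4.1), so they are unavailable for patients who never reply.

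**Item loss is easily overstated.** One might multiply over all 36 RAND-36 items (0.98^36 = 48.3%) and conclude that about half the data are unusable. Section 1.4.1 scores the RAND-36 as eight separate scales, so one skipped item affects one scale. The protocol also cites scoring instructions for that instrument that are not at hand, so no scoring gap can be asserted for it.

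**Conclusion.** The concern holds in limited form. The reason given for not imputing is invalid. Because the analyses named use observed values only, the primary estimates at all three time points and both group comparisons are exposed to selective response.

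The documents do not show that such bias exists, how large it is or which way it runs. In the assumed example with response depending on ICU stay, it is 1.5 points (22.5% against 24.0%) and recoverable from data the study collects. Under assumed symptom-dependent response it could be larger, in either direction, and only partly correctable.

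This should be corrected, since the rule governs the primary estimates and the change is cheap. It does not invalidate the study, and the available-case results remain worth reporting.

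**What to change.** In section 1.4.3, delete the stated reason and replace the sentence with the following rules:

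- Keep the available-case results.
- Report response by wave and by COVID-19 and ICU group, and compare responders with non-responders on record data as far as the review board's waiver allows.
- Beside the unweighted estimates, report with 95% confidence intervals either response-weighted estimates, using the record variables listed in section 1.4.1, or multiple-imputation or likelihood-based repeated-measures estimates for patients with at least one completed wave.
- Handle skipped items by each instrument's own scoring rule. Do not apply a half-scale rule to the EQ-5D, whose value is a weight for a health state defined by all five dimensions.
- State the missing-at-random assumption, and say that response driven by symptoms beyond the recorded variables would not be fully corrected.

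The cost is extra analysis work and somewhat wider intervals. No new data collection is needed.

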**1.5 Methods: Monitoring**

**1.5.1. Data Monitoring**

No data safety monitoring was needed for this study

**1.5.2. Risk for participants**

No risk applies when patients participate in this study. Data will be processed and analyzed anonymously and will not be retraceable to the individual patient.

**1.6 Ethics and dissemination**

**1.6.1 Research Ethics Approval**

This protocol was reviewed and approved by the Local Institutional Review Boards of the participating study site. The need for ethics approval by an accredited Medical Ethics Committee and written informed consent was waived due to the observational nature of the study.

**1.6.2 Protocol amendments**

Modifications to the protocol which impacted on the conduct of the study, potential benefit of the patient or affected patient safety, including changes of study objectives, study design, patient population, sample sizes, study procedures, or significant administrative aspects were formal amendments to the protocol. Such amendment will be approved by the Institutional Review board prior to implementation and notified to the health authorities in accordance with local regulations.

**1.6.3 Consent or Assent**

The need for written informed consent was waived by the Local Institutional Review Board Informed consent for the use of data gathered using the questionnaires will nevertheless be asked in the first questionnaire. Patients consent by returning a filled-out questionnaire or opt-out by returning an empty questionnaire.

**1.6.4 Confidentiality**

All study-related information will be stored securely at the study site. Returned questionnaire will be stored in locked file cabinets in areas with limited access. All reports, data collection, process, and administrative forms were identified by a coded ID [identification] number only to maintain participant confidentiality. All local databases were secured with password-protected access systems. Forms, lists, logbooks, and any other listings that link participant ID numbers to other identifying information were stored in a separate, locked file in an area with limited access.

Participants’ study information was not be released outside of the study without the written permission of the participant.

**1.6.5 Declaration of interests**

The authors of the protocol have no competing interests.

**1.6.6 Access to data**

All collaborating investigators had full access to view the data concerning their study site during the study. All collaborating investigator had full access to the final data sets. All data was password protected.

